### Concealment mechanism {16b}

As stated above, participants will be allocated to treatment or control groups using block randomization after being recruited by audiology clinics. Allocation will be done by the study coordinator in a sequentially numbered fashion using opaque, sealed envelopes. The study coordinator will only know one patient outcome of intervention at a time to inform the MI therapist and patient. The recruiting audiologists will be blinded to study group allocation and do not have access to the allocation sequence. Only the MI therapist and study coordinator will be informed of patient group allocation after recruitment.

### Implementation {16c}

Participating audiologists and the trained clinic staff will enroll eligible participants. Assignment to the intervention and control groups will be done independently by the study coordinator.

## Assignment of interventions: blinding

### Who will be blinded {17a}

Audiologists and the investigators at the time of outcome data collection will not be blinded to study group allocation. The analysis team will receive aggregated data obtained for control and intervention groups. Study participants will become aware of their group allocation as the study progresses, but they will be asked not to reveal their group allocation to the treating audiologist or other investigators.

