### Objectives {7}

The primary objective is to determine the efficacy of one-on-one MI in increasing adherence to HA use in new adult clients in the short and long terms. The secondary objective is to determine if there are adverse effects associated with one-on-one MI.

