#### Criteria for discontinuing or modifying allocated interventions {11b}

The intervention and control groups are expected to have a low risk of adverse events. Interim visits not previously scheduled may be required for other reasons such as HA malfunctions. All events of accidental injury or participant withdrawal of consent during the trial will be recorded.

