### Outcomes {12}

#### Primary outcomes

The primary outcome is the inter-group difference in average hours of HA use at 1, 3, 6, and 12 months post-intervention aimed at assessing the early and long-term effect of the intervention. This is a quantitative measure recorded by the HAs data-logging feature.

The secondary outcomes are differences in inter-group average participant-completed questionnaire (IOI-HA) [21] scores at 1, 3, 6, and 12 months post-intervention and reported complications. The IOI-HA is an established rigorous patient reported measure for HA effectiveness [22, 23].

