### Participant timeline {13}

Figure 1 demonstrates the participant timeline for this study. Participating audiologists will screen potential candidates in their normal day-to-day work. Signed consent and baseline assessment will be obtained from those who meet inclusion criteria and agree to participate in the study. All participants will have a 1-month follow-up after the initial assessment with an audiologist in-person or via telehealth where IOI-HA questionnaires will be administered, and HA data-logging will be accessed. Those in the intervention group will also undergo a 30-min one-on-one MI session after the 1-month follow-up visit and the details will be provided by the study coordinator. Subsequent follow-up visits will be conducted at 3, 6, and 12 months where participants will complete the IOI-HA questionnaire and their HA data-logging will be accessed.

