### Plans to promote participant retention and complete follow-up {18b}

A member from the audiology clinic will complete all forms along with participants to ensure the completeness of the forms. These standardized forms have been revised to improve understandability to ensure completeness. In the event of withdrawal prior to completion, any data collected up to the withdrawal time point will be retained and included for data analyses. A SPIRIT flow diagram demonstrates the data collection in the intervention and control groups (Table 2) [25].

**Table 2 Tab2:** Schedule of enrollment, interventions, and assessments

**Timepoint**	**Study period**											
	**Enrollment**		**Allocation**		**Post-allocation**				**Close-out**			
	***−t***_***1***_ −48 months to −1 day		***t***_***0***_ Day 0		***t***_***1***_ 1 month		***t***_***2***_ 3 months		***t***_***3***_ 6 months		***t***_***4***_ 12 months	
	**T**^**a**^	**C**^**b**^	**T**^**a**^	**C**^**b**^	**T**^**a**^	**C**^**b**^	**T**^**a**^	**C**^**b**^	**T**^**a**^	**C**^**b**^	**T**^**a**^	**C**^**b**^

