### Adverse event reporting and harms {22}

After participants have provided consent and enrolled in the study, adverse events will be collected and recorded until the end of the study period. Adverse events that occur after consent is signed, but before receiving the study intervention will be reported as not related to our intervention. Any serious adverse event that occurs will be reported to the institutional review board (IRB) and will be documented.

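### The request that participants conceal their allocation from follow-up staff has no exception for harms and may discourage reports of problems attributed to MI, in the MI arm only

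*Protocol article*

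**What the plan says.** All references are to the protocol article.

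- **Harms are an aim of the trial.** Objectives {7}: "The secondary objective is to determine if there are adverse effects associated with one-on-one MI". The secondary outcomes in Outcomes {12} are IOI-HA "scores at 1, 3, 6, and 12 months post-intervention and reported complications".
- **Participants are asked to conceal allocation.** Who will be blinded {17a}: "they will be asked not to reveal their group allocation to the treating audiologist or other investigators". No exception is written.
- **The same section describes those staff as unblinded.** "Audiologists and the investigators at the time of outcome data collection will not be blinded to study group allocation". Concealment mechanism {16b}, however, says that only the MI therapist and the coordinator learn allocation after recruitment.
- **Contacts after the session.** Participant timeline {13} sets visits at 3, 6 and 12 months, "where participants will complete the IOI-HA questionnaire and their HA data-logging will be accessed". Under {11a}, investigators access the data-logging and audiologists record the hours. Under {11c}, investigators telephone those who miss visits to explore barriers. Under {18b}, "A member from the audiology clinic will complete all forms along with participants to ensure the completeness of the forms".
- **What is recorded as harm.** Item {11b}: "All events of accidental injury or participant withdrawal of consent during the trial will be recorded". Adverse event reporting and harms {22} is broader: "adverse events will be collected and recorded until the end of the study period".

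**The concern.** MI is a counselling session, so a plausible harm is non-serious, such as distress or upset after the call. A participant who links that harm to the session can hardly describe the link without mentioning the session, and mentioning it reveals allocation. The people they meet at follow-up, or who telephone after a missed visit, are the people from whom they were asked to conceal it.

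The deterrent is one-sided. Control participants are asked to conceal their group too, but they have no MI session to blame for an event. Any silence produced by the request therefore falls on the MI arm and pulls the secondary objective towards no adverse effects. Few events are expected ({11b} calls the risk low), so losing one or two reports could change what the trial concludes about harm.

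**Working it through.** **Step 1. Who is inside the request and who is outside it**

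| Person | Covered by the {17a} request? | Contact after the MI session, as the article gives it |
|---|---|---|
| Treating audiologist | Yes | Follow-up visits; records hours ({11a}, {13}) |
| Investigators | Yes | Data-logging access ({11a}); calls after missed visits ({11c}) |
| Clinic staff completing forms | Not named, but work beside the audiologist | All forms ({18b}) |
| Study coordinator | No; knows allocation ({16b}) | None scheduled; kept out of data collection ({16a}, Discussion); acts on serious events ({17b}) |
| MI therapist | No; knows allocation ({16b}) | None scheduled after the session |

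The scheduled contacts after MI lie with people inside the request. The two people outside it are not named as a route for non-serious harms.

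**Step 2. What the request blocks**

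- An event reported without mention of MI: not blocked.
- A serious event: not blocked in effect, since {17b} lets the principal investigator and the coordinator unlock the code.
- A non-serious event that the participant attributes to MI, told to an audiologist or investigator: this goes against the request. It is also directly relevant to {7}.

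**Step 3. Sensitivity to silence (assumed rates)**

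The article gives no adverse event rate and no probability of reporting. The only input taken from it is the arm size in Sample size {14}: 45 per arm with a 50% dropout allowance, 45/(1 − 0.5) = 90 per arm, as stated. Let n be the number in the MI arm, p the true rate of MI-related harm and r the share of those affected who report it.

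- Expected reports = n × p × r
- Chance of no report = (1 − p × r)^n

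| n | p (assumed) | Expected, r = 1 | Expected, r = 0.5 | No report, r = 1 | No report, r = 0.5 |
|---|---|---|---|---|---|
| 90 | 2% | 1.8 | 0.9 | 0.98^90 = 0.16 | 0.99^90 = 0.40 |
| 90 | 5% | 4.5 | 2.25 | 0.95^90 = 0.01 | 0.975^90 = 0.10 |
| 45 | 2% | 0.9 | 0.45 | 0.98^45 = 0.40 | 0.99^45 = 0.64 |
| 45 | 5% | 2.25 | 1.12 | 0.95^45 = 0.10 | 0.975^45 = 0.32 |

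The rows with n = 45 show the MI arm if the full 50% dropout allowance is used up. The table shows how sensitive a low-count outcome is to silence. It is no evidence that silence will occur.

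**The case against.** A reader might infer that reporting any adverse effect breaks the instruction, that harms will therefore be under-reported, and that the secondary objective cannot be answered. The documents do not support this:

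- The request covers group allocation, not events. Distress or anxiety can be reported without naming the session.
- Item {22} collects adverse events to the end of the study with no limit by type. The shorter list in {11b} belongs to the discontinuation criteria and should not be read as the whole harms plan.
- The coordinator and the MI therapist are outside the request. The coordinator also e-mails session instructions to MI participants ({18a}), so a line of contact exists.
- Who collects adverse events, and on what form, is a detail that an article commonly leaves to the full protocol.
- Every silence rate above is assumed. Even with half silent, the chance of at least one report among 90 is 0.90 at a 5% rate and 0.60 at 2%.
- If audiologists and investigators really are unblinded, as {17a} says, participants have little to conceal from them.

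These points limit the concern to non-serious events that participants attribute to MI, and make it a risk rather than a prediction. They do not remove it. The request is stated without an exception, and it touches the very reports that {7} seeks. The unblinding statement does not settle the matter either. If it is right, the request protects little and an exemption costs almost nothing. If it is an error, concealment is meant to hold and the deterrent is real.

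**Conclusion.** The concern holds in limited form. The non-disclosure request has no stated exception for harms and covers the staff who conduct the contacts after MI. It may discourage non-serious reports attributed to MI, in that arm only, and so bias the secondary harms objective towards no adverse effects. The size cannot be derived from the documents, and the illustration rests wholly on assumed rates of 2% and 5% with half of those affected silent. The data-logged hours and IOI-HA comparisons are not affected by this point. A separate and firmer matter in the same place is that {17a} calls audiologists and investigators unblinded, while {16b} and the request itself presume that they do not know allocation. This is a worthwhile low-cost improvement rather than a flaw that threatens the trial.

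**What to change.** 1. **Exempt harms.** State in {17a} and in the participant instruction that the request does not apply to reporting any adverse event or concern.
2. **Name a route.** Say that such reports may also go to the coordinator or the MI therapist, who already know allocation.
3. **Ask both arms the same question.** Add one identical adverse-event item, including emotional distress, to the online survey at 1, 3, 6 and 12 months. The participant completes it privately, outside the clinic-assisted forms of {18b}. Store it with the survey data. The coordinator may be alerted for safety but should not be the sole collector, because {16a} and the Discussion keep that person out of data collection and complications are an outcome. The 1-month answer precedes the session and fits the rule in {22} on events before the intervention.
4. **Reconcile the text.** Align {11b} with the broader adverse events of {22}, and reconcile the unblinded statement in {17a} with {16b} and with the request.

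Cost: an ethics amendment, a sentence or two in the participant instruction, one survey item taking a few seconds, and occasional disclosure of allocation when an event is reported. No visit or staff is added.

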### Procedure for unblinding if needed {17b}

In the unlikely event where a participant encounters a serious adverse event, the principal investigator (PI) and the study coordinator will unlock that participant’s allocation code to investigate the event.

## Data collection and management

### Plans for assessment and collection of outcomes {18a}

Consented participants will be instructed about the study and its procedures. At the initial visit, data collection forms, including the email addresses of each participant, will be filled and collected by a trained audiology clinic assistant. This data will be securely stored on a password-protected device and transferred to the study coordinator and PI for long-term use and protection.

Outcome assessments of data-logged hearing hours and IOI-HA questionnaires will be performed at 1-, 3-, 6-, and 12-month time points after hearing aid fitting.

#### Pre-intervention assessment at 1 month

Participants in both groups will continue to be contacted by their audiology clinics as required for standard care at the above-mentioned time point. Participants in the MI intervention group will attend a virtual one-on-one counseling session after their 1-month follow-up from hearing aid fitting. Teleconferencing software will be used to organize this meeting and instructions will be provided via email to each participant or a family member by study coordinator. The total time is anticipated to be approximately 30 min. This session will be hosted by a practicing MI therapist who will explore and elicit motivation in the participants to use their HAs for more hours.

#### Post-intervention assessment at 3-, 6-, and 12-month follow-ups

Post interventions will be performed at 3-, 6-, and 12-month follow-ups from hearing aid fitting. During these follow-ups, in addition to standard care, participants will have the number of data-logged hearing hours per day extracted from their hearing device automatic data-logging feature and will be asked to complete the online IOI-HA questionnaires. The IOI-HA has been previously tested for its validity, reliability, and sensitivity [22, 23]. There have been suggestions that item 5 on the IOI-HA contributes inconsistently [22, 23]. However, the introspective subscale (items 1, 2, 4, and 7) of the IOI-HA was found to have a Cronbach’s alpha of 0.85 [23]. It has previously been used in other hearing aid outcome research [6].

### Plans to promote participant retention and complete follow-up {18b}

A member from the audiology clinic will complete all forms along with participants to ensure the completeness of the forms. These standardized forms have been revised to improve understandability to ensure completeness. In the event of withdrawal prior to completion, any data collected up to the withdrawal time point will be retained and included for data analyses. A SPIRIT flow diagram demonstrates the data collection in the intervention and control groups (Table 2) [25].

**Table 2 Tab2:** Schedule of enrollment, interventions, and assessments

**Timepoint**	**Study period**											
	**Enrollment**		**Allocation**		**Post-allocation**				**Close-out**			
	***−t***_***1***_ −48 months to −1 day		***t***_***0***_ Day 0		***t***_***1***_ 1 month		***t***_***2***_ 3 months		***t***_***3***_ 6 months		***t***_***4***_ 12 months	
	**T**^**a**^	**C**^**b**^	**T**^**a**^	**C**^**b**^	**T**^**a**^	**C**^**b**^	**T**^**a**^	**C**^**b**^	**T**^**a**^	**C**^**b**^	**T**^**a**^	**C**^**b**^
**Enrollment:**												
Eligibility screen	X	X										
Informed consent	X	X										
Allocation			X	X								
**Intervention:**												
One-on-one MI					X							
Standard care						X	X	X	X	X	X	X
**Assessments:**												
Baseline assessment												
PTA			X	X								
WRS			X	X								
Primary outcomes												
Mean hours hearing aid used					X	X	X	X	X	X	X	X
IOI-HA score					X	X	X	X	X	X	X	X

*T* Treatment group, *C* Control group, *MI* Motivational interviewing, *PTA* Pure tone audiometry, *WRS* Word recognition score, *IOI-HA* International Outcome Inventory for Hearing Aids

### Data management {19}

To minimize data-entry errors, the data entry will be double-checked for errors or omissions by a study investigator blinded to group allocations. All consent forms and data will be managed by the study coordinator for secure documentation. Data will be stored in password-protected encrypted computers and physically held in patient charts.

### Confidentiality {27}

Participants will have the opportunity to have an informed discussion with study investigators regarding the trial when being screened for eligibility and prior to being consented. Participant will be assigned to a unique identification number to maintain the patient confidentiality.

### Plans for collection, laboratory evaluation, and storage of biological specimens for genetic or molecular analysis in this trial/future use {33}

N/a. There are no biological specimens that will be collected in this study.

## Statistical methods

### Statistical methods for primary and secondary outcomes {20a}

Descriptive Statistics will be used to summarize patient demographics. Independent samples *T*-tests will be used to compare continuous variables such as PTA averages, word recognition scores, and data-logged hearing hours between groups. Chi-squared test will be used to determine the degree of association between categorical variables such as patient-reported outcome, sex, and age group. A univariate linear regression will be run with demographic variables and data-logged hearing hours. Pearson’s correlations will also be used to measure the strength of associations between data-logged hearing aid use hours and self-reported measures via the IOI-HA questionnaire. Data will be analyzed using SPSS (Version 25).

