### Trial design {8}

This study will be a multi-center, prospective, randomized patient-blind controlled trial and employ a between-subject, pre- and post-tests design with a treatment and control group. It has been designed to be a superiority trial assessing motivational interviewing compared to standard audiological care. The SPIRIT (Standard Protocol Items: Recommendations for Interventional Trials) reporting guidelines were used to develop the methodology.

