#### Intervention description {11a}

Patients allocated to the intervention group will attend a 30-min maximum one-on-one MI session hosted by a practicing MI therapist via Zoom at 1 month after the initial visit. Participants will also receive standard audiological care delivered at in-person clinic visits.

All control and intervention participants will be asked to attend 4 follow-up visits after the initial baseline assessment at 1, 3, 6, and 12 months. At follow-up visits, all participants will complete online International Outcome Inventory for Hearing Aids (IOI-HA) questionnaires and the study investigators will access each participant’s HA data-logging feature to determine the mean number of hours HAs were activated. Audiologist(s) will record the daily average hours of use based on the number of days since the last reading. All data will be entered using a secure online survey tool.

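### Data-logged hours are compared by unadjusted t-tests, and the 1-month reading, taken before the MI session, is treated as an outcome rather than a baseline: a loss of precision, not of validity

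*Protocol article*

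**What the plan says.** All references are to the protocol article.

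- **Analysis.** Statistical methods {20a} states that independent-samples t-tests "will be used to compare continuous variables such as PTA averages, word recognition scores, and data-logged hearing hours between groups". The only regression is this: "A univariate linear regression will be run with demographic variables and data-logged hearing hours". No section names a change score, ANCOVA or a repeated-measures model.
- **Design.** Trial design {8} says the trial will "employ a between-subject, pre- and post-tests design with a treatment and control group".
- **The 1-month visit.** Participant timeline {13} states: "All participants will have a 1-month follow-up after the initial assessment with an audiologist in-person or via telehealth". Data-logging is accessed at that visit. The intervention arm "will also undergo a 30-min one-on-one MI session after the 1-month follow-up visit". The data collection plan heads this visit "Pre-intervention assessment at 1 month".
- **What a reading covers.** Intervention description {11a}: "Audiologist(s) will record the daily average hours of use based on the number of days since the last reading". The 1-month value therefore describes use in the first month, and later readings cover later periods.
- **Outcome definition.** Outcomes {12}: "The primary outcome is the inter-group difference in average hours of HA use at 1, 3, 6, and 12 months post-intervention". Table 2 also lists the 1-month hours under primary outcomes.

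**The concern.** New users have no hearing aid hours before fitting. The 1-month reading is therefore the only value of the primary outcome that can be had before MI, and it is already scheduled in both arms. The planned t-test does not use it to adjust later comparisons. The regression does not fill the gap: it relates hours to demographic variables one at a time, so it neither estimates the treatment effect nor brings in earlier hours.

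Two things follow. Part of the variation in later hours that early use could explain stays in the error term, in a trial that counts on only 45 evaluable participants per arm. And if 1 month is tested as a primary time point, the arms are compared on a reading that, as scheduled, MI cannot have affected.

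**Working it through.** **1. Inputs.** From Sample size {14}: standardized difference 0.6, 5% significance, 80% power, 45 per arm, 50% dropout, 180 in total. The correlation r between 1-month and later hours is not in the protocol. It is assumed here at 0.3, 0.5 and 0.7.

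**2. The plan's own figure.**
- Normal approximation, two-sided: n = 2 × (1.960 + 0.842)² / 0.6² = 43.6, so 44 per arm.
- t-based calculation: 44.6, so 45 per arm, with power 80.4% at 45.
- A one-sided test would need 35 and does not match.
- Dropout: 45 / (1 − 0.5) = 90 per arm, 180 in total.

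The stated size is reproduced. It is the size for an unadjusted two-sample t-test.

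**3. Gain from adjustment.** With the same SD and r in both arms and a linear relation, adjusting for 1-month hours multiplies the residual variance by (1 − r²). Hence:
- effective difference = 0.6 / √(1 − r²)
- noncentrality = effective difference × √(45/2), with 2 × 45 − 3 = 87 degrees of freedom for ANCOVA
- equivalent unadjusted n = 45 / (1 − r²)
- smallest difference detectable with 80% power (normal approximation) = (1.960 + 0.842) × √(2/45) × √(1 − r²)

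| r (assumed) | 1 − r² | Power at 45 per arm | Equivalent unadjusted n per arm | Detectable difference (SD) |
|---|---|---|---|---|
| none (t-test) | 1 | 80.4% | 45 | 0.59 |
| 0.3 | 0.91 | 83.9% | 49 | 0.56 |
| 0.5 | 0.75 | 90.2% | 60 | 0.51 |
| 0.7 | 0.51 | 97.6% | 88 | 0.42 |

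**4. Chance imbalance in early use.** The standard error of the between-arm difference in 1-month hours is √(2/45) = 0.211 SD. An imbalance of one standard error moves the unadjusted later difference by r × 0.211: 0.06, 0.11 or 0.15 SD at r = 0.3, 0.5 or 0.7. The t-test's standard error already allows for this, so it is imprecision and not bias. It is the same loss as in step 3, seen another way.

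**5. Is the 1-month reading a legitimate covariate?** Table 2 puts allocation at day 0 and the 1-month reading after it, so adjustment is safe only if allocation cannot have influenced that reading.
- *In favour:* Participant timeline {13} and the 1-month assessment section place MI after the visit, and the Discussion says masking lasts until participants are told of their MI appointment.
- *Left open:* Concealment mechanism {16b} has the coordinator inform the patient but gives no time. Who will be blinded {17a} says participants become aware of their group as the study goes on. Intervention description {11a} places MI at 1 month after the initial visit. No section requires the reading to come before the notice.

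**6. The label on 1 month.** Outcomes {12} counts 1 month as post-intervention, while the data collection plan calls the same visit pre-intervention. Nor can the Outcomes wording mean a separate reading one month after MI, since Table 2 has no such visit. The sections cannot both stand.

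**The case against.** The strongest reply is that nothing is broken. The t-test is unbiased under randomization, holds its error rate and is the test on which the sample size rests, so {14} and {20a} agree. All of this stands. A reader might infer that the planned test is biased or that the trial is underpowered as designed; the documents support neither.

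A reader might also infer that the pre-test is discarded, or that the plan prescribes a separate t-test at every visit. The first is not so: the 1-month hours are analysed, but as an outcome. The second is only an inference from the four time points in {12}; {20a} does not say how visits are handled. Nor will every participant have the reading. It is scheduled for all, but 50% dropout is allowed for.

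Three further objections carry weight:
- The covariate is measured after allocation. If participants learned of the MI appointment before the reading, early use in that arm could shift, and adjustment could then bias an effect that the unadjusted test estimates without bias. This makes the remedy conditional.
- The size of the gain rests on an assumed correlation and is small at r = 0.3. Some positive correlation is reasonable for repeated measures of one behaviour in the same person, but the protocol gives no value.
- An analysis plan that is not shown might add adjustment. That weakens the point without removing it, because this document names the t-test for hours and itself gives the 1-month visit conflicting labels.

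**Conclusion.** The point holds as one of efficiency and internal consistency. The protocol fixes an unadjusted comparison although a pre-intervention value of the primary outcome is already scheduled in both arms, and it labels that value post-intervention in the outcome definition.

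The cost is precision: the planned analysis forgoes between about 4 percentage points of power (r = 0.3) and 17 (r = 0.7) at the stated effect and size. This rests on the assumed r, on equal SDs and a linear relation in both arms, and on the 1-month reading being unaffected by allocation. The change is worth making, but the trial's validity and stated sample size do not depend on it.

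**What to change.** 1. **Prespecify the adjusted analysis.** Make the primary comparison an ANCOVA or mixed model of 3-, 6- and 12-month hours on arm, with 1-month hours as covariate. Report the adjusted difference with its 95% confidence interval. Treat the IOI-HA score likewise, with its 1-month value as covariate. Keep the t-test as a supportive analysis. Fix this before any comparison of outcomes between arms, including the second interim analysis.
2. **Reconcile the sections.** Bring Outcomes {12} and Table 2 into line with Participant timeline {13} and the 1-month assessment section, so that 1 month is the baseline and not a primary outcome time point.
3. **Protect the covariate.** State that the 1-month reading is recorded before a participant is told of the MI appointment. Where that order was not kept, do not use the reading as a covariate, or show the unadjusted result as a sensitivity analysis.

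**Cost.** No new data are needed, and the named software can fit the model. Steps 2 and 3 go beyond analysis wording: they change the outcome definition and fix a procedural order, so a formal amendment with review board approval under {25} should be expected.
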